### 5.3 Recruitment procedures:

Patients who are eligible for the trial will be recruited at the Outpatient unit in Pham Ngoc Thach (PNT) Hospital, where new cases of tuberculosis are diagnosed and receive their full treatment under direct observation (see Appendix 1). The appointed clinical trial nurse and counsellor will liaise with the doctors responsible for managing tuberculosis to identify patients who have been diagnosed with pulmonary tuberculosis and HIV, who have had a CD4 count analysis. Patients will be given full information on the objectives and methods of the trial. Patients will be given a copy of the information sheet to read before the screening appointment. If, at time of screening, patients present with an intercurrent opportunistic infection requiring specific concomitant treatment, they will not be included in the study.

Patients meeting eligibility criteria after screening will be enrolled in the trial and started on 300mg RBT in combination with INH, PZA, and EMB, corresponding to day 0 of the trial (visit 1).

### 5.4 Follow-up procedures:

In the Vietnamese TB Control Programme, patients come to District TB Units (DTU) every day to receive anti-TB drugs under the supervision of health workers. All patients involved in the study will come to the Outpatient Clinic at PNT Hospital to take their drugs, to receive specific training on HIV and TB as well as scheduled appointments. PNT Hospital will hold this organization according to the requirements of the study. Those who miss their scheduled appointment will be contacted within 24 hours or a home visit made to obtain information on their condition. Participants will be asked to return after 14 days

After fourteen days of RBT therapy, patients will return and will undergo the **first pharmacokinetic analysis (PK1)** as described below, as well as safety bloods and clinical evaluation. After completion of PK1 analysis, all participants will commence their randomized RBT-ART combination according to prior randomization.

1. After 3 weeks of ART, patients will complete a week 5 visit (visit 3) corresponding to **PK2** and then switch RBT doses. After a further 3 weeks of ART, patients will complete a week 8 visit corresponding to **PK3**. After completion of PK3, all participants will be referred to national program to complete SCC and continue ART according to standard program care. At the end of tuberculosis treatment, patients will have a blood taken for haematological and biochemical tests, HIV viral load and CD4 count - as well as a sputum for smear and microbiology. The results of these tests will be made available for the clinician in charge of the patient in the National Program.

2. Participants who have failed to achieve viral suppression (<250 copies/ml) will be offered to have an HIV genotypic resistance test performed in order to help clinician to propose an adapted ART second line.
3. All participants who give consent will participate in the pharmacogenomics sub-study.

#### 5.5 Adverse Events (AEs) and Severe Adverse Events (SAEs):

Patients will be assessed for the development of AEs and SAEs at each scheduled clinic and PK visit, and at any unscheduled visits.

An SAE is defined as any untoward medical occurrence that:

- results in death
- is life threatening
- requires inpatient hospitalization or prolongation of existing hospitalization
- results in persistent or significant disability/incapacity
- Pregnancy
- is a congenital anomaly/birth defect

SAEs will be reported within 24 hrs of the investigator becoming aware of the event. The report will be made by fax or e-mail to [name], or designee, at The Union Head Office in Paris, and a full report will be subsequently completed for each SAE. [name] will be responsible for reporting all SAEs to ANRS within 7 days. Full procedures for reporting SAE's are outlined in Appendix 2.

At enrolment (day 0), a full eye examination will be carried out, including assessment of visual acuity, pupillary reflexes, eye movements and fundoscopy. Focused questions will be asked at screening and each visit to determine if eye pain, eye redness, sensitivity to light or blurred vision is present and an external eye examination will be carried out to facilitate the early detection of uveitis (a recognized AE associated with RBT). Patients will be warned to report any ocular symptoms. Patients reporting eye symptoms will be referred for full ophthalmologic examination.

Each participant will also be asked about arthralgia at each visit. Regular laboratory test monitoring will allow early detection of neutropenia, renal insufficiency, hepatitis. Patients will be encouraged to report to the clinic at any time during the follow-up period if they feel unwell, in order to maximise the capture of AEs. Any death will be registered and all efforts will be made to identify the likely cause(s) of death. AEs occurring during the study will be evaluated by the investigator and graded according to the Division of Aids table for grading the severity of adult and paediatric adverse events. The relationship between the trial medications and each AE/SAE will be investigated and graded with regard to likelihood of causality.

In the event of hospitalization the trial physician will liaise directly with the appropriate medical staff. The designated trial physician assesses all participants who are inpatients on a regular basis. Particular attention will be given to the detection and management of IRIS. Other possibilities (drug fever, treatment failure, TB recurrence, drug resistance, opportunistic infection) need to be ruled out with all appropriate evaluations including multiple blood cultures, urine, chest x-ray, sputa testing and other procedures. If IRIS is suspected, symptomatic therapy (anti-inflammatory agents) will be initiated at the discretion of the study clinician. A separate IRIS reporting form will be used to ensure adherence to a standardized diagnosis and treatment protocol.

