### 1.2 Screening

Subjects attending the screening appointment who have volunteered to participate in the study will be requested to sign an informed consent form in accordance with international GCP standards. They will then undergo a full clinical evaluation and the following screening tests to determine eligibility for enrolment (blood samples taken will be approximately 25 ml):

- Full clinical examination, including ophthalmologic examination
- Full Blood Count (FBC) - Haemoglobin, platelet and differential white cell counts.
- Urea and electrolytes (U&E) - Sodium, potassium, urea, creatinine, bicarbonate
- Liver Function Tests (LFT) - Total bilirubin, aspartate and alanine aminotransferase, albumin, alkaline phosphatase
- Amylase
- HIV test
- CD4 count
- Urinary pregnancy test
- Urinalysis
- Chest X-ray (CXR)

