#### **3.2 Secondary outcomes:**

1. The pharmacokinetics of LPV/r in combination with two doses of RBT determined by the  $AUC_{0-12}$ .
2. The tuberculosis cure determined by sputum smear examination in line with the National TB Programme Guidelines
3. Proportion of participants with any grade 3 or 4 AE or SAE.

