**Table 2: Trial Schedule**

|                                                  | Screening | Visit 1 | Visit 2        | Visit 3 | Visit 4 | Visit 5              |
|--------------------------------------------------|-----------|---------|----------------|---------|---------|----------------------|
|                                                  | Day -2    | Day 0   | Week 2         | Week 5  | Week 8  | Week 24  |
| Patient Information                              | X         |         |                |         |         |                      |
| Informed Consent                                 | X         |         |                |         |         |                      |
| Inclusion/Exclusion                              | X         | X       |                |         |         |                      |
| Randomisation                                    |           | X       |                |         |         |                      |
| Clinical History                                 | X         |         |                |         |         |                      |
| Physical examination                             | X         | X       | X              | X       | X       | X                    |
| Adverse Event Screening                          |           | X       | X              | X       | X       | X                    |
| Karnofsky score                                  | X         |         |                |         |         |                      |
| CD4 Count                            | X         |         |                |         |         | X                    |
| HIV antibody test                                | X         |         |                |         |         |                      |
| HIV viral load                       |           |         | X              |         |         | X                    |
| FBC                                  | X         |         | X              | X       |         | X                    |
| U and E                              | X         |         |                |         | X       |                      |
| LFT                                  | X         |         | X              | X       | X       | X                    |
| Amylase                              | X         |         |                |         | X       |                      |

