| Pregnancy Test                                   | X         |         |                |         | X       |                      |
| Urinalysis                                       | X         |         |                |         | X       |                      |
| Chest X-ray                                      | X         |         |                |         | X       | X                    |
| Sputum Smear and Culture                         | X         |         |                |         | X*      | X                    |
| Susceptibility Testing                           | X         |         |                |         |         | X                    |
| Pharmacokinetic analysis                         |           |         | PK1            | PK2     | PK3     |                      |
| Optional Pharmacogenomics sampling   |           |         | X  |         |         |                      |
| Start Rifabutin/INH/Ethamb/PZA                   |           | X       |                |         |         |                      |
| Stop Rifabutin/INH/Ethamb/PZA & start Rifamp/INH |           |         |                |         | X       |                      |
| Start D4T/3TC-LPV/rtv                            |           |         | X              |         |         |                      |
| Stop LPV/rtv & start Efavirenz                   |           |         |                |         | X       |                      |
| Stop Rifamp/INH                                  |           |         |                |         |         | X                    |

1, 2, 3. The tests included are listed in section 1.2. The volumes of blood required for each set of tests are FBC: 4ml, Biochemical tests: 4ml, CD4 count: 4ml, Viral load: 8ml;

Pharmacogenomics (optional and for patients who give specific consent): 8ml

last visit can be done between week 24 and week 26.

\* Sputum smears in smear-positive PTB patients

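### Section 5.5 relies on laboratory monitoring to detect renal insufficiency early, but Table 2 schedules the first on-treatment creatinine at Week 8, when the study regimen stops

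*Protocol*

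**What the plan says.** Section 5.5 of the protocol states: "Regular laboratory test monitoring will allow early detection of neutropenia, renal insufficiency, hepatitis". The scheduled test that measures renal function is defined in Section 1.2: "Urea and electrolytes (U&E) - Sodium, potassium, urea, creatinine, bicarbonate".

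Table 2 marks U&E at screening and at Week 8. Amylase and urinalysis follow the same pattern. Liver function tests (LFT) are marked at screening and at Weeks 2, 5, 8 and 24, and the full blood count (FBC) at screening and at Weeks 2, 5 and 24. U&E, LFT and amylase carry the same footnote, which gives a volume: "Biochemical tests: 4ml".

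Section 5.4 adds two general statements. At Week 2 the first pharmacokinetic day is accompanied by blood tests, "as well as safety bloods and clinical evaluation", with no panel named. At the end of tuberculosis treatment "patients will have a blood taken for haematological and biochemical tests", again with no panel named. For Week 5 it says: "After 3 weeks of ART, patients will complete a week 5 visit (visit 3) corresponding to PK2 and then switch RBT doses". It mentions no safety bloods at that visit.

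The safety aim is secondary objective 4, on the safety and toxicity of RBT with antiretroviral therapy in the initial phase. Secondary outcome 3 is "Proportion of participants with any grade 3 or 4 AE or SAE".

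**The concern.** The sentence in Section 5.5 makes laboratory monitoring, not symptoms, the means of finding renal insufficiency early. One post-baseline value, taken as the study drugs are withdrawn, is neither regular nor early.

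Two things are at stake. The first is ascertainment: a raised creatinine that causes no symptoms, or that resolves before Week 8, will not enter the safety data. The second is interpretation: by Week 8 every patient has taken both RBT-LPV/r doses, so a renal abnormality first seen then could have arisen under either dose or in the two-week RBT lead-in. Week 5 is the one visit that could separate the first randomised dose from the second, and no renal test is scheduled there.

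**Working it through.** The plan states no figure to reproduce, so the check is a count of the marks in Table 2 and of the intervals between them.

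**Scheduled post-baseline measurements** (Table 2; no laboratory safety test is marked at Day 0)

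| Test | Week 2 | Week 5 | Week 8 | Week 24 | Total of 4 |
|---|---|---|---|---|---|
| LFT | yes | yes | yes | yes | 4 |
| FBC | yes | yes | no | yes | 3 |
| U&E | no | no | yes | no | 1 |
| Amylase | no | no | yes | no | 1 |
| Urinalysis | no | no | yes | no | 1 |

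Of the three conditions named in Section 5.5, hepatitis is covered by four LFT readings, neutropenia by three FBC readings and renal insufficiency by one U&E reading. Urinalysis does not fill the gap, because it has the same two time points as U&E.

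**Interval to the first on-treatment U&E.** Screening is Day -2 and Week 8 is Day 8 × 7 = 56. The gap is 56 − (−2) = 58 days. It contains the start of RBT (Day 0), the start of antiretroviral therapy (Week 2) and the switch of RBT dose (Week 5). Table 2 also places the stop of RBT and of LPV/r at Week 8.

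**Position relative to the dose periods.** The first randomised period runs from Week 2 to Week 5 and the second from Week 5 to Week 8. Table 2 has no U&E at the start or the end of the first period, and one at the end of the second.

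**Most generous reading of Section 5.4.** Suppose the unspecified Week 2 bloods include U&E. The gap then runs from Week 2 (Day 14) to Week 8 (Day 56): 56 − 14 = 42 days, still spanning both dose periods with nothing at Week 5. Suppose the end-of-treatment biochemistry also includes U&E. That value falls at Week 24, 24 − 8 = 16 weeks after RBT and LPV/r have stopped, so it says little about either dose.

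**With U&E at Weeks 2 and 5 as well as Week 8.** The gaps up to Week 8 are 14 − (−2) = 16 days, 35 − 14 = 21 days and 56 − 35 = 21 days. The longest falls from 58 to 21 days, and each dose period has a reading at its start and its end.

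**The case against.** The other side has several fair points.

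- **Section 5.4 may already require more.** The Week 2 and end-of-treatment bloods are undefined and could include U&E. It is therefore Table 2, rather than the whole protocol, that plainly omits these visits. This stands for Weeks 2 and 24. It does not help at Week 5.
- **Events are also found clinically.** Adverse events are assessed at every scheduled, pharmacokinetic and unscheduled visit, patients are encouraged to attend if unwell, and a persistent abnormality would still show at Week 8. This stands. It would be wrong to infer that renal events in the first dose period are simply missed; the exposure is limited to silent or transient changes. Even so, Section 5.5 gives the early-detection task to laboratory tests.
- **No dose comparison of safety is planned.** A reader might infer that a within-patient comparison of the two doses has been lost, leaving 16 patients on one dose against 16 on the other at Week 8. The protocol supports neither step. Outcome 3 is counted per participant, objective 4 contains no dose contrast, and the paired comparisons in Section 5.9 concern pharmacokinetic measures. Nor would 16 against 16 separate the doses, since all patients have had both by Week 8.
- **Pancreatic events are not promised.** A reader might extend the contradiction to amylase, which has the same schedule. Section 5.5 names neutropenia, renal insufficiency and hepatitis only, so the amylase schedule contradicts nothing.
- **The shared sample is an inference.** The footnote gives a volume for each set of tests; it does not say in terms that one tube serves LFT, U&E and amylase. This stands as a caution on the cost of the remedy.

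**Conclusion.** The inconsistency is real and confined to renal monitoring. Section 5.5 claims early detection through regular tests, while Table 2 provides one post-baseline U&E, 58 days after screening and at the end of the study regimen. On any reading of Section 5.4, Week 5 has no scheduled renal test. Silent or transient renal abnormalities before Week 8 may go undetected, and a Week 8 abnormality cannot be attributed to one RBT-LPV/r dose.

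The effect is a modest weakening of ascertainment for objective 4 and outcome 3. It rests on the assumption that graded laboratory abnormalities count towards outcome 3. The protocol does not say so there, but the inclusion criteria speak of grade 3 or 4 laboratory findings, so laboratory results are treated as gradable. The documents give no expected rate of renal abnormality, so the number of events affected cannot be estimated. The primary outcome, rifabutin exposure, is untouched. Severity is minor.

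**What to change.** Reconcile Table 2 with Sections 5.4 and 5.5, and name the panels meant by the Week 2 safety bloods and the end-of-treatment biochemistry. Narrowing the sentence in Section 5.5 to match Table 2 would remove the contradiction but would leave the measurement gap.

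The inexpensive way to close the gap is to add U&E to the biochemical sample that Table 2 already schedules for LFT at Weeks 2 and 5, and at Week 24 as Section 5.4 implies. Amylase could be added to the same sample as an option; no statement in the protocol requires it.

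The cost is at most 32 × 2 = 64 further U&E panels for Weeks 2 and 5, or 32 × 3 = 96 with Week 24. No extra visit is needed and, going by the shared footnote, apparently no extra blood draw; the laboratory should confirm that the 4 ml sample is sufficient.

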#### 5.6 Microbiology procedures:

At screening and at the end of the trial sputum will be tested by smear examination and culture, using Lowenstein-Jensen solid medium. Baseline isolates will be preserved in glycerol enriched media and their drug susceptibility compared with any isolate obtained at the end of therapy. Patients diagnosed with multidrug resistant tuberculosis (MDR-TB) will be withdrawn immediately from the trial and referred for initiation of MDR-TB treatment to the appropriate structure as soon as the second line treatment is available in Viet Nam.

#### 5.7 Immuno-virological procedures:

Blood samples will be collected at time of screening for a confirmatory HIV test and CD4 count. These tests will be performed at Pasteur Institute HCMC. In addition, samples for HIV viral load quantification will be tested using a commercial assay. Aliquots of all samples will be preserved for subsequent evaluation of genotypic resistance to ART.

#### 5.8 Pharmacological procedures and assays:

Participants will be admitted to the clinical pharmacokinetic facility at Pham Ngoc Thach Hospital for the evening prior and after PK sampling on 3 separate occasions and meals and snacks will be standardized between the three PK studies. **PK1** will be conducted once steady state dosing has been established. This will be achieved by keeping patients on RBT during the first 2 weeks of the SCC intensive phase and carrying out PK analysis after two weeks of the intensive phase therapy have been completed. **PK2** and **PK3** will be completed 3 and 6 weeks after PK1, at which time steady state dosing of the ARV regimen has been established. Blood samples will be drawn into lithium-heparin coated tubes at each of the times after drug administration illustrated in Table 3. Five millilitres of blood will be collected for RBT assays alone and eight millilitres for RBT and ARV assays.

**Table 3:** Table showing the sampling times for each arm at each pharmacokinetic visit

|                                   | PK 1   | PK2      |          | PK3      |          |
|-----------------------------------|--------|----------|----------|----------|----------|
| Visit number                      | 2      | 3        |          | 4        |          |
| Arms                              | A, B   | A        | B        | A        | B        |
| Sampling relative to morning dose | Assays |          |          |          |          |
| -0.5 to 0 hrs                     | RBT    | RBT, LPV | RBT, LPV | RBT, LPV | RBT, LPV |
| 2 hrs                             | RBT    | RBT, LPV | RBT, LPV | RBT, LPV | RBT, LPV |
| 3 hrs                             | RBT    | RBT, LPV | RBT, LPV | RBT, LPV | RBT, LPV |
| 4 hrs                             | RBT    | RBT, LPV | RBT, LPV | RBT, LPV | RBT, LPV |
| 5 hrs                             | RBT    | RBT, LPV | RBT, LPV | RBT, LPV | RBT, LPV |
| 6 hrs                             | RBT    | RBT, LPV | RBT, LPV | RBT, LPV | RBT, LPV |
| 8 hrs                             | RBT    | RBT, LPV | RBT, LPV | RBT, LPV | RBT, LPV |
| 12 hrs                            | RBT    | RBT, LPV | RBT, LPV | RBT, LPV | RBT, LPV |
| 24 hrs                            | RBT    | RBT      | RBT      | RBT      | RBT      |
| 48 hrs                            | RBT    |          |          |          | RBT      |
| Total Blood Sampled               | 45 ml  | 50 ml    | 45 ml    | 45 ml    | 50 ml    |

NB: For the drug assays RBT = rifabutin. LPV= Lopinavir.

Intensive sampling will be used over the dosing interval in order to adequately characterize the pharmacokinetic measures of importance (AUC, Cmax). The samples will be immediately stored in crushed ice for a maximum of 1 hour, until centrifugation and separation of plasma on site. Separated plasma will be transferred into 2 separate polypropylene (microcentrifuge) tubes, each containing approximately 1 ml of plasma before immediate storage in the Pham Ngoc Thach laboratories at -80C. The exact times of specimen collection will be recorded in the case record forms. Aliquots of the plasma samples will be transferred on dry ice to the Department of Biological Analysis at the Pasteur Institute HCMC by door-to-door transport, for PK analyses. The concentrations of rifabutin, its major metabolite 25-deacetyl-rifabutin and LPV/r will be determined by High Pressure Liquid Chromatography (HPLC). Validated methods will be developed according to GLP in conjunction with Kremlin-Bicêtre Hospital Pharmacology laboratory in Paris, and a QA procedure will be set between Pasteur Institute HCMC and the University of Cape Town Clinical Pharmacology Division.

